**Commonly administered pregnancy screening tests**

It is feasible to use common pregnancy screening tests such as Alpha fetoprotein (AFP) usually administered within narrow gestational-age windows to determine start of pregnancy episode. An assessment in Optum of the accuracy of these screening tests in determining length of pregnancy episode was conducted and of the 4 most commonly performed tests in the table below, AFP and nuchal ultrasound produced enough accuracy. However, the second algorithm in Margulis et al. [[2](#_ENREF_2)] attempted to determine beginning of pregnancy with screening test claims such as alpha fetoprotein in live births and only 45.4% of estimated gestational age at birth were within 1 week of the hospital discharge estimate; they had better success with outcome-specific estimates. For this reason, in our algorithm, we will discard any AFP or nuchal ultrasound calculated start dates that create an episode shorter or longer than the minimum and maximum allowed episode for that outcome in Table 3.

| **Table 3: Median length of pregnancy episode in days when commonly administered pregnancy screening tests are used to infer episode start date** | | | | |
| --- | --- | --- | --- | --- |
| **Pregnancy screening test** | **Clinical gestational age at which test is recommended in weeks** | **Optum Gestational age used at date of test in weeks** | **Optum median length of pregnancy in days with start date calculated from screen test** | **Comment** |
| **Alpha fetoprotein** | 15-20 | 17.5 | 276.5 | present in 1/3 live births;Q3=284 days |
| **Amniocentesis** | 15-20 | 17.5 | 258 | too few done in population |
| **Nuchal ultrasound** | 11.5-13.85 | 12.65 | 279 | Present in 16% live births;Q3=285 days |
| **Gestational Diabetes screening** | 24-28 | 26 | 272 | glucose screenings done prior to 26 week screen;Q3=386 days |

**Pregnancy Episode Start Date Calculation**

To calculate pregnancy episode start date possible start dates will be assigned in the following hierarchy (final start date chosen will be first one assigned in hierarchy):

**Step 1:** LMP (last menstrual period) date as start of pregnancy episode:

1. If LMP records exists between (larger of maximum term allowed subtracted from outcome date or prior outcome date plus retry count) and minimum term allowed subtracted from outcome date then LMP becomes the pregnancy start date
2. If there are more than one LMP records in the live birth window, use the latest so as not to grab a LMP record from an earlier pregnancy episode
3. ~50% of CPRD live births will have an LMP value (median pregnancy length 280 days using LMP date as start of episode); no US claims live births will

**Step 2:** GEST (gestational age in weeks) date as start of pregnancy episode:

1. In CPRD, for GEST record use string_as_value from observation table or in CPRD or US CLAIMS use gest_value from pregnancy concept file, whichever is present. Only use GEST values between 0 and 42 weeks.
2. If GEST record date-(GEST value*7) +1 exists between (larger of maximum term allowed subtracted from outcome date or prior outcome date plus retry count) and minimum term allowed subtracted from outcome date then GEST record date-(GEST value*7) +1 becomes the pregnancy start date.
3. If there are more than one GEST records in the allowed time window, use the latest so as not to grab a GEST record from an earlier episode
4. ~28% of CPRD live births will have a GEST value and not a LMP value with a median pregnancy length 279 days (in CPRD GEST codes are used for any outcome in the additional file); 1.4% of Optum live births will have a GEST value with a median pregnancy length 230 days (in OPTUM GEST codes are used primarily to record a premature birth)

**Step 3:** NULS (nuchal ultrasound) date as start of pregnancy episode:

1. If NULS date-89 exists between (larger of maximum term allowed subtracted from outcome date or prior outcome date plus retry count) and minimum term allowed subtracted from outcome date then NULS date-89 becomes the pregnancy start date.
2. If there are more than one NULS records in the allowed time window, use the first so as to use the NULS date that is most likely the recommended date in clinical guidelines rather than a repeat test.

**Step 4:** AFP (alpha fetoprotein test) date as start of pregnancy episode:

1. If AFP date-123 exists between (larger of maximum term allowed subtracted from outcome date or prior outcome date plus retry count) and minimum term allowed subtracted from outcome date then AFP date-123 becomes the pregnancy start date.
2. If there are more than one AFP records in the allowed time window, use the first so as to use the AFP date that is most likely the recommended date in clinical guidelines rather than a repeat test.

**Step 5:** Outcome specific estimates:

1. If at least one PREM (premature term pregnancy), POSTT (post term pregnancy) or FT (full term pregnancy) record exists between (larger of maximum term allowed subtracted from outcome date or prior outcome date plus retry count) and 30 days after outcome date then categorize pregnancy as PREM, POSTT or FT.
2. If combinations of PREM, POSTT, FT records exist in this time window, categorize pregnancy in this order: 1) PREM if present, 2) POSTT if present, 3) FT if present.
3. Based on Table 4, choose an outcome specific gestational age estimate based on outcome and term and subtract from outcome date to obtain a pregnancy start date. If prior outcome date plus retry count is greater than outcome date minus outcome specific gestational age estimate then pregnancy start date becomes prior outcome date plus retry count.

**Step 6**: Choose final pregnancy start date:

1. Choose the best pregnancy start date (first one assigned in steps 1-5).
2. If a PCONF (pregnancy confirmation), AGP (antenatal GP visit) or OTEST (other pregnancy test) category records exist between (larger of maximum term allowed subtracted from outcome date or prior outcome date plus retry count) and minimum term allowed subtracted from outcome date and is prior to the best start date as calculated in the prior 5 steps then the first found PCONF, AGP or OTEST becomes pregnancy start date.

Table 4 provides outcome specific gestational age estimates for all outcomes for premature, post and full term pregnancies. These outcome specific gestational age estimates were obtained from Hornbrook et al.[[1](#_ENREF_1)] and Margulis et al. and were validated by in-house clinical experts and should represent average gestational times for the outcomes and terms.

| **Table 4: Outcome Specific Gestational Age Estimates in Days** | | | | |
| --- | --- | --- | --- | --- |
| **Outcome** | **PreTerm** | **PostTerm** | **FullTerm** | **NoData** |
| **LB** | 245 | 285 | 280 | 280 |
| **SB** | 196 | 285 | 280 | 196 |
| **DELIV** | 245 | 285 | 280 | 280 |
| **TRO** | 56 | 56 | 56 | 56 |
| **ECT** | 56 | 56 | 56 | 56 |
| **AB** | 70 | 70 | 70 | 70 |
| **SA** | 70 | 70 | 70 | 70 |

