## OVERVIEW OF STUDY DESIGN

### Study Design

This study follows a retrospective cohort design. 7 pregnancy episode outcome cohorts will be created and characterized from women with any pregnancy markers or outcomes:

- Live birth (at least one)
- Stillbirth
- Delivery-Live birth or stillbirth
- Trophoblastic Disease
- Ectopic pregnancy
- Induced abortion
- Spontaneous abortion

Women are allowed multiple pregnancy episodes and the unit of analysis will be the pregnancy episode. Valid pregnancy outcomes for each patient will be chosen using an algorithm that utilizes an outcome assessment hierarchy, i.e. live births are assessed for validity first for each patient, any that are too close to another live birth are discarded. Still births for the same patient are then assessed to see if they are too close to all prior assessed live births and any other valid still births etc. Start dates will be assigned using pregnancy markers in a hierarchical fashion also (last menstrual period date records considered as start of pregnancy first, next considered are gestational age estimate records, etc.) See page 12 for a full description of the algorithm.

In medical practices, pregnancy episodes traditionally begin with the last menstrual period date and end with the birth outcome date as defined by the algorithm. The first trimester is defined as week 1-13, 2^nd^ trimester week 14-26 and 3^rd^ trimester week 27-40. For our episodes, the first two weeks of the first trimester will be defined as a pre-exposure period as conception most likely does not happen prior to this time.

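### The gestational-age rule in Step 2 accepts a value of 0 weeks, which sets the pregnancy start one day after the record that documents the pregnancy

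*Protocol*

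**What the plan says.** The rule is in the protocol, Pregnancy Episode Start Date Calculation, Step 2. It limits the usable values: "Only use GEST values between 0 and 42 weeks". If the calculated date falls in the allowed window, "GEST record date-(GEST value*7) +1 becomes the pregnancy start date". The window runs from the "larger of maximum term allowed subtracted from outcome date or prior outcome date plus retry count) and minimum term allowed subtracted from outcome date". The terms come from Table 2; for a live birth they are 301 days (maximum) and 161 days (minimum). For several records the rule is: "If there are more than one GEST records in the allowed time window, use the latest".

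The final start is the first date assigned in Steps 1 to 5, so a GEST date yields only to a last-menstrual-period (LMP) date and precedes nuchal ultrasound (Step 3), AFP (Step 4) and the Table 4 estimates (Step 5). Step 6 can move the start earlier. If a pregnancy confirmation (PCONF), antenatal GP visit (AGP) or other pregnancy test (OTEST) record lies in the window and precedes the chosen date, "then the first found PCONF, AGP or OTEST becomes pregnancy start date". GEST records are not in that list.

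Study Design dates episodes from the LMP and adds that "the first two weeks of the first trimester will be defined as a pre-exposure period as conception most likely does not happen prior to this" point.

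**The concern.** A record of gestational age is itself evidence that the woman is already pregnant, so the start it yields should not be later than the record. With a value of 0 it is. A 0 also fits poorly with the protocol's own convention: counted from the LMP, week 0 lies inside the two weeks that Study Design places before likely conception. If 0 is in practice a placeholder or an empty field (an assumption; the protocol does not say), the rule would treat it as a real measurement.

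The one-day overshoot is trivial. What matters is that the start is tied to the date of the record instead of to the LMP, so the episode loses roughly the whole time from LMP to that record. Correct or plausible start date is one of the three measures in Validation Procedures, and the distribution of pregnancy terms by outcome is a planned output under Descriptive Analyses.

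**Working it through.** **Inputs.** Formula, value range, window and tie rule: Step 2. Minimum and maximum terms: Table 2. Term estimates: Table 4. The days of the example records are assumed for illustration.

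**1. Formula against the protocol's own figures.** For a value g recorded r days before the outcome, episode length = r + 7g − 1. If the value is recorded on the outcome date (r = 0, assumed), 40 weeks gives 7×40 − 1 = 279 days and 33 weeks gives 7×33 − 1 = 230 days. These match the medians stated in Step 2 for CPRD (279) and Optum (230). The formula as printed is therefore consistent with them, but the medians cannot be derived from inputs in the document.

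**2. Start relative to the record.** Start − record date = 1 − 7g.
- g = 0: +1 day, after the record
- g = 1: −6 days
- g = 2: −13 days

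The start falls after the record only when g < 1/7 week; among whole weeks, only at 0.

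**3. Which zeros pass the term check.** With g = 0 the length is r − 1, so a record passes when minimum + 1 ≤ r ≤ maximum + 1, with no prior-outcome limit:

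| Outcome | Table 2 min–max | Passing r (days before outcome) |
|---|---|---|
| LB | 161–301 | 162–302 |
| SB, DELIV | 140–301 | 141–302 |
| TRO | 42–112 | 43–113 |
| ECT | 42–84 | 43–85 |
| AB | 42–168 | 43–169 |
| SA | 28–133 | 29–134 |

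**4. Live birth at 280 days, LMP on day 0.** A 0 recorded on day d gives length 280 − (d + 1). It passes if this is at least 161, so d ≤ 118. At d = 70 the start is day 71 and the length 209 days, below even the 245 days that Table 4 uses for a preterm live birth. Had the 0 been rejected and no other dating record existed, Table 4 would have given 280 days.

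**5. Displacement of a valid record.** Take a value of 8 on day 56 and a 0 on day 84, same birth. The first gives start 56 − 56 + 1 = day 1, length 279. The second gives start day 85, length 195. Both lie within 161–301, and the tie rule takes the later record, so the start moves 84 days.

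**6. Step 6.** Take the 0 on day 70 and an antenatal visit on day 56. The start moves from day 71 to day 56, and the length becomes 224 days. A visit on day 70 itself gives start day 70 and length 210. The start is no longer after the record, but it is still 56 or 70 days late.

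**7. How many episodes.** The protocol gives no frequency. Step 2 puts CPRD live births with a GEST value and no LMP value at about 28%. If a share f of these were dated by a 0, the affected share of CPRD live births would be 0.28f. For f from 0.1% to 2%, a purely assumed range, that is 0.03% to 0.6%, before any repair by Step 6.

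**The case against.** Much limits the effect, and these limits stand:

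- An LMP date in the window takes precedence, and the protocol expects one in about half of CPRD live births.
- The term check rejects a 0 recorded near the outcome. Recorded on the outcome date, it gives a start one day after the outcome and fails for every outcome. Step 2 says that Optum GEST codes mainly record premature birth, which suggests recording near delivery.
- The tie rule works both ways. A surviving 0 in a live birth is at least 162 days before the outcome, so any later valid GEST record in the window replaces it.
- Step 6 may move the start back, as shown.
- The limits of the range might be meant as exclusive, and no document shows that any record carries a 0.

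It can also be said that checks exist: term distributions are reviewed, and clinical personnel assess start dates in sampled profiles. These could reveal the problem but do not remove the rule. With 100 CPRD live-birth profiles (50 plus the extra 50) and the assumed 0.03% to 0.6%, the chance of seeing at least one case, 1 − (1 − p)^100, is about 3% to 43%.

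Three stronger readings are tempting, and the document does not support them.

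- A reader might infer that every 0 shifts the start by the full elapsed pregnancy. The limits above show otherwise.
- A reader might infer from the 28-day minimum in Table 2 that values below 4 weeks should be barred. That figure is the shortest gestation at a spontaneous abortion, not the earliest time at which gestational age can be recorded. A value of 3 in a pregnancy that continues contradicts nothing in Table 2.
- A reader might take the CPRD medians of 279 days (GEST) and 280 days (LMP) as proof that the added day is an error. They come from different groups of births, and nuchal dating in Optum, with no added day, also has a median of 279 (Table 3). The nuchal and AFP constants are rounded midpoints (12.65×7 = 88.55, used as 89; 17.5×7 = 122.5, used as 123), so they set no day-count convention either.

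**Conclusion.** The point holds in a narrow form. Read in the ordinary way, Step 2 admits a value of 0 and then produces a start date that contradicts the record it is taken from. Neither the term check nor Step 6 reliably prevents this, and such a date outranks three other dating sources. In an affected live birth the error can be several weeks or more: 71 days in the day-70 example, with a term birth appearing as 209 days. The number of affected episodes cannot be stated from the protocol and may be very small or nil. The conclusion assumes that the limits of the range are inclusive and that zeros exist in the data or in the concept file. It does not extend to values of 1 to 3 weeks or to the added day as such. It is a minor defect, worth correcting because the correction is so cheap.

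**What to change.** In Step 2, accept only GEST values greater than 0 and up to 42 weeks. Add a check that rejects any calculated start later than its own GEST record; this also catches fractions below 1/7 week. A rejected record should pass the episode on to the next valid GEST record in the window or, if there is none, to Steps 3 to 5. With whole weeks, the smallest accepted value then gives a start 6 days before the record.

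State also whether the added day in Step 2 is an intended day-count convention, since Steps 3 to 5 do not use it. This is a clarification, not a correction.

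The cost is one changed limit, one added comparison and a sentence in the protocol. The only whole-week value lost is 0. A count of zero-valued GEST records in each database would supply the frequency that the protocol lacks.

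### Step 2 accepts a gestational age of 0 weeks, which starts the pregnancy the day after its own record; the Table 2 window blocks this only near the outcome

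*Protocol*

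**What the plan says.** In the Protocol, Pregnancy Episode Start Date Calculation, Step 2 takes the start date from a GEST record.

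- Item 1 sets the only filter on the value itself: "Only use GEST values between 0 and 42 weeks".
- Item 2 gives the formula: "GEST record date-(GEST value*7) +1 becomes the pregnancy start date", provided that date lies in the allowed window. The window opens at the outcome date minus the maximum term, or at the prior outcome date plus the Table 2 interval before a second pregnancy if that is later. It closes at the outcome date minus the minimum term.
- Item 3 deals with several records: "If there are more than one GEST records in the allowed time window, use the latest". The stated aim is to avoid a record from a previous pregnancy.

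The steps form a hierarchy: "final start date chosen will be first one assigned in hierarchy". LMP therefore outranks GEST, and GEST outranks nuchal ultrasound, AFP and the Table 4 estimates. Step 6 then moves the start earlier if a PCONF, AGP or OTEST record in the window precedes it.

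Item 4 shows that the step is widely used in CPRD. It gives, as an approximate figure, "28% of CPRD live births will have a GEST value and not a LMP value with a median pregnancy length 279 days".

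**The concern.** A filter on gestational age is there to keep out values that cannot date a pregnancy. This one lets 0 through, and the formula then dates the start after the record that reports the pregnancy. If the zero is not a true 0-week value, the start is too late by about the gestation already elapsed, and a term pregnancy can be given the length of a very preterm one.

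Step 2 ranks above the nuchal scan, AFP and term codes, so a later step that would have given a sensible date is never used. Because item 3 prefers the latest record, a zero may also displace a valid gestational age in the same pregnancy.

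Determining the pregnancy start is part of the primary objective, and start-date correctness is one of the three validation measures. The Study Design section also defines trimesters by week from the start, so a late start mislabels them.

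**Working it through.** **Inputs.** Formula: start = R − 7 × GEST + 1, where R is the record date (Step 2 item 2). Maximum and minimum terms from Table 2: live birth 301 and 161 days; spontaneous abortion 133 and 28 days. Days are counted from a true start at day 0. The examples use a 280-day live birth and a 70-day spontaneous abortion, which are the Table 4 no-data estimates, and assume no prior outcome narrows the window.

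**The plan's own figure.** If GEST = 40 is recorded on the outcome date (an assumption; the Protocol does not say when GEST is recorded), the length is 7 × 40 − 1 = 279 days. This matches the stated CPRD median.

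**What a zero does.** GEST = 0 gives start = R + 1. For comparison, GEST = 1 gives R − 6.

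**Which zeros pass the window.**
- Live birth: outcome − 301 ≤ R + 1 ≤ outcome − 161, so R lies 302 to 162 days before the birth. In a 280-day pregnancy the last accepted day is 280 − 162 = 118. The length is 280 − (R + 1) = 279 − R, running from 279 days (R = 0) to 161 days (R = 118).
- Spontaneous abortion at day 70: R + 1 ≤ 70 − 28 = 42, so R ≤ 41. Lengths run from 69 to 28 days.
- A zero less than 162 days before a live birth, or less than 29 days before a spontaneous abortion, is rejected.

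**One zero, no other GEST record.** Recorded on day 84 of a 280-day pregnancy: start on day 85, length 279 − 84 = 195 days.

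**A zero together with a valid record (280-day live birth).** The Protocol does not define *latest*, so three readings were tried: (i) latest calculated start in the window; (ii) latest record date among records whose calculated start is in the window; (iii) as (ii), with the record date also in the window. Each valid record below gives a start on day 1 and a length of 279 days.

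| Records | (i) | (ii) | (iii) |
| --- | --- | --- | --- |
| 8 weeks on day 56, then 0 on day 84 | 195 | 195 | 195 |
| 0 on day 70, then 12 weeks on day 84 | 209 | 279 | 279 |
| 0 on day 70, then 40 weeks on day 280 | 209 | 279 | 209 |

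In the first row the zero wins under every reading, and 279 − 195 = 84 days are lost. In the other rows the result depends on the reading.

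**Step 6.** If the first antenatal visit was on day 56, the start moves from day 85 to day 56 and the length becomes 280 − 56 = 224 days, still well short of 279. A visit on the same day as the zero moves the start by one day only.

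**Trimesters.** With the start at day 85 instead of day 1, the 13 weeks labelled first trimester are weeks 13 to 25 counted from day 1.

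**The case against.** The strongest reply is that nothing in the Protocol says zeros occur or serve as placeholders. That stands. A reader might infer that any zero must be a placeholder, because the Study Design section treats the first two weeks as a pre-exposure period "as conception most likely does not happen prior to this time". The inference does not follow. That remark concerns conception, and the same section counts pregnancy from LMP, so 0 weeks is a legitimate value on the scale. A genuine zero dated at LMP would put the start one day late and do no harm. Blank fields are largely covered as well, because item 1 uses whichever source value is present.

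Second, the minimum term already removes zeros recorded at or near delivery, and the 279-day median is compatible with GEST often being recorded there. This also stands: only zeros from early or mid-pregnancy matter.

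Third, a reader might conclude that a zero always overrides a valid value. The table shows that it does not; this depends on order, timing and the meaning of *latest*.

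Fourth, there are partial safeguards: Step 6, the review of term distributions by outcome, the profile review of start dates in CPRD and Optum, and independent code review. Except for Step 6 they can only detect the problem, and they may miss a rare one. Code review confirms agreement with the Protocol, which permits the zero.

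Finally, *between* could be read as exclusive. That would also drop 42 weeks, although Table 2 allows a live birth up to 301 days (43 weeks), so the inclusive reading is the natural one.

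**Conclusion.** The point holds as a boundary error in a rule that the Protocol itself fixes: a GEST value of 0 is accepted and yields a start after its own record, and the term window stops this only near the outcome. When the zero is not genuine, the error in a single episode can be large (84 days in the example with two records), Steps 3 to 5 cannot correct it, and Step 6 repairs it only partly and only if an earlier PCONF, AGP or OTEST record exists. Episodes with an LMP date in the window, about half of CPRD live births by the Protocol's own figure, are unaffected.

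The overall effect is unknown. One might be tempted to multiply the 28% of CPRD live births dated by GEST by some assumed share of zeros. The documents give no such share, and the product would ignore both the window and Step 6, so no percentage of births should be claimed. The conclusion rests on the inclusive reading of the range and, for any harm beyond one day, on the existence of zeros that are not true 0-week values. Severity is minor.

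**What to change.** In Step 2 item 1, state that only GEST values greater than 0 and up to 42 weeks are used. Apply this before item 3 chooses among records, so that a zero cannot displace a valid value, and report the number of zeros dropped in each database. That count would also show whether the problem exists.

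The cost is one sentence and one program condition. A genuine 0-week record dated at LMP would be discarded; the episode would then be dated by another GEST record or by Steps 3 to 5, so no episode is lost. In the first example the start returns to day 1 and the length to 279 days.

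The change does not remove other implausibly low values: 1 week recorded on day 84 gives a start on day 84 − 7 + 1 = 78 and a length of 202 days.

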###### 2nd Step in the Pregnancy Episode Algorithm: Assignment of Start Dates

In the pregnancy episode algorithm time periods need to be defined for various elements in order to calculate pregnancy start date. In Table 2 below the following time periods for each outcome are defined:

- Maximum pregnancy term - amount of time to search back from the outcome for all pregnancy markers. This time period should be the longest possible gestation period for an outcome so as to capture early markers.
- Minimum pregnancy term - Shortest possible gestational period for each outcome.
- Number of days a 2^nd^ pregnancy is possible after the outcome – This time window indicates how many days after the outcome specified another pregnancy may be initiated.

All time windows were estimated from research specific to each outcome and validated by in-house clinical experts.

| **Table 2: Time windows in days necessary to calculate pregnancy episode start date** | | | |
| --- | --- | --- | --- |
| **Outcome** | **Maximum Pregnancy Term** | **Minimum Pregnancy Term** | **Days 2nd pregnancy possible after outcome** |
| **LB** | 301 | 161 | 28 |
| **SB** | 301 | 140 | 28 |
| **DELIV** | 301 | 140 | 28 |
| **TRO** | 112 | 42 | 14 |
| **ECT** | 84 | 42 | 14 |
| **AB** | 168 | 42 | 14 |
| **SA** | 133 | 28 | 14 |

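### Steps 2 to 4 check the calculated start date but not the date of the record, so nuchal-scan, AFP and gestational-age records dated after the outcome can set the episode start

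*Protocol*

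**What the plan says.** The Protocol section Pregnancy Episode Start Date Calculation ranks the sources of a start date: LMP, GEST, NULS, AFP, then the Table 4 estimate by outcome.

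- **Step 2 (GEST):** "If GEST record date-(GEST value*7) +1 exists between (larger of maximum term allowed subtracted from outcome date or prior outcome date plus retry count". The upper bound is the outcome date less the minimum term. The limit on values is the same for every outcome: "Only use GEST values between 0 and 42 weeks". With several records, "If there are more than one GEST records in the allowed time window, use the latest".
- **Step 3 (NULS):** "If NULS date-89 exists between (larger of maximum term allowed subtracted from outcome date or prior outcome date plus retry count"), with the upper bound "and minimum term allowed subtracted from outcome date then NULS date-89 becomes the pregnancy start date".
- **Step 4 (AFP):** "If AFP date-123 exists between (larger of maximum term allowed subtracted from outcome date or prior outcome date plus retry count"), with the same upper bound.

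The paragraph on commonly administered screening tests also discards NULS and AFP starts that give an episode outside the permitted length. That again tests the calculated start.

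Two other places bear on the point. The definitions above Table 2 say "Maximum pregnancy term - amount of time to search back from the outcome for all pregnancy markers". Step 5 limits the date of the record itself: premature, post-term and full-term codes count up to 30 days after the outcome.

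**The concern.** A window on the calculated start limits the record date only indirectly, through the number of days subtracted. Where that number exceeds the minimum term for the outcome, the rule accepts records dated after the pregnancy is said to have ended.

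A scan or AFP test that implies an ongoing pregnancy after the recorded end cannot validly date that episode. Either the outcome record was wrong, or the test is misdated or unrelated. A GEST value entered after the outcome is read as gestation on the day of entry, so the start moves later by the delay.

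Determining episodes from start to end is the primary objective, and the share of episodes with a correct or plausible start date, by outcome, is one of the validation measures. Code that follows the text literally would also pass the second programmer's check, which is made against the protocol.

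**Working it through.** **Offsets.** Table 3 places the nuchal scan at 12.65 weeks and AFP at 17.5 weeks. 12.65 × 7 = 88.55 and 17.5 × 7 = 122.5, which round up to the protocol's 89 and 123. For GEST the offset is 7 × value − 1.

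**Inverting the rule.** Set the outcome at day 0. The condition −max ≤ record − offset ≤ −min gives

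record date from (offset − max) to (offset − min).

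A prior outcome can only move the lower end later. With the terms in Table 2:

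| Outcome | Max / min term | NULS dates accepted | AFP dates accepted |
|---|---|---|---|
| LB | 301 / 161 | −212 to −72 | −178 to −38 |
| SB, DELIV | 301 / 140 | −212 to −51 | −178 to −17 |
| TRO | 112 / 42 | −23 to +47 | +11 to +81 |
| ECT | 84 / 42 | +5 to +47 | +39 to +81 |
| AB | 168 / 42 | −79 to +47 | −45 to +81 |
| SA | 133 / 28 | −44 to +61 | −10 to +95 |

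For ECT, for example, 89 − 84 = +5 and 89 − 42 = +47; 123 − 84 = +39 and 123 − 42 = +81.

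**Could these tests belong to the next pregnancy?** Table 2 allows a new pregnancy from day 14 after TRO, ECT, AB or SA. At the earliest recommended ages in Table 3, its scan would fall at 14 + 11.5 × 7 = 94.5 days and its AFP test at 14 + 15 × 7 = 119 days. Both lie beyond the accepted ranges (at most +61 and +95), so properly timed tests from a next pregnancy do not explain them.

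**Effect on the start date.** A record on day r gives an episode of 89 − r days (NULS) or 123 − r days (AFP). The comparison is with the Table 4 default, taking only post-outcome records and before Step 6:

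| Outcome | Default | NULS episode length | AFP episode length | Start against default |
|---|---|---|---|---|
| ECT | 56 | 84 to 42 | 84 to 42 | 28 earlier to 14 later |
| TRO | 56 | 88 to 42 | 112 to 42 | NULS 32, AFP 56 earlier; 14 later |
| AB | 70 | 88 to 42 | 122 to 42 | NULS 18, AFP 52 earlier; 28 later |
| SA | 70 | 88 to 28 | 122 to 28 | NULS 18, AFP 52 earlier; 42 later |

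**GEST.** A record can post-date the outcome when 7 × value − 1 exceeds the minimum term. That happens from 24 weeks for LB, 21 for SB and DELIV, 7 for TRO, ECT and AB, and 5 for SA.

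- ECT, 8 weeks (offset 55): 55 − 84 = −29 to 55 − 42 = +13. Records before the outcome qualify.
- ECT, 12 weeks (offset 83): −1 to +41.
- ECT, 13 weeks (offset 90): +6 to +48. From here upward, every qualifying record is after the outcome.
- LB, 40 weeks (offset 279): 279 − 301 = −22 to 279 − 161 = +118. A gestation-at-birth value entered on day +118 puts the start at 118 − 279 = −161 instead of −279, which is late by the full 118 days unless Step 6 intervenes.

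**The case against.** **Searching back.** The definition of maximum term speaks of searching back from the outcome for all pregnancy markers, and the lay summary counts nuchal ultrasound dates as markers. A programmer could take this as a limit on record dates. It is a fair reading, but Steps 2 to 4 do not carry it, while Step 5 states its own record-date limit. Under that reading Step 3 could never date an ECT episode, nor Step 4 an ECT or TRO episode, and the steps do not say so. The passages need reconciling either way.

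**Rule-out screen.** TRO, ECT and SA records are dropped if an antenatal visit, pregnancy confirmation or complication record lies within 42 days. This removes some of the false outcomes. It does not look at NULS, AFP or GEST records, and AB has no such screen.

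**Step 6.** An earlier confirmation, antenatal-visit or other-test record inside the window replaces the chosen start. In the 118-day example, any such record from −301 up to −161 would do so. This stands as a partial remedy for starts that are too late; it cannot move a start later.

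**Median for GEST.** The protocol reports a median length of 279 days for CPRD live births dated by GEST. That equals 7 × 40 − 1, a 40-week value dated on the day of birth, so typical entries look timely. A median does not show how many are late.

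**Stronger readings to avoid.** A reader might infer that for ectopic pregnancy every record usable in Steps 2 to 4 must be post-outcome. That is untrue of GEST values of 0 to 12 weeks. Nor do the documents show that the roughly 28% of CPRD live births with GEST and no LMP are wrongly dated; that is the share using the source, not the share affected. The 47, 81 and 95 days are positions of records, not errors in the start date.

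**Conclusion.** The rules are wrong as written and should be corrected. For NULS and AFP the defect is confined to TRO, ECT, AB and SA; live births, stillbirths and deliveries cannot be affected. It is complete in three cells: NULS for ECT, AFP for ECT and AFP for TRO, where every qualifying record follows the outcome yet outranks Table 4. The Table 2 window bounds the consequence, and for ECT the start differs from the 56-day default by at most 28 days earlier or 14 later.

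For GEST the defect can touch any outcome, with a start late by the entry delay where the value describes gestation at the outcome and Step 6 finds nothing earlier. The rule that prefers the latest record favours such an entry over an earlier sound one.

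This rests on a literal reading of Steps 2 to 4. How often post-outcome records occur is not given, so no share of misdated episodes can be stated.

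**What to change.** **Steps 3 and 4.** Add the condition that the NULS or AFP record must be dated on or before the outcome date. This brings both steps into line with the search-back definition. It leaves TRO NULS −23 to 0, AB NULS −79 to 0 and AFP −45 to 0, and SA NULS −44 to 0 and AFP −10 to 0. Step 3 then falls away for ECT, and Step 4 for ECT and TRO. If no earlier source applies, the Table 4 estimate is used. No separate exclusions are needed, and births are unchanged.

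**Step 2.** A plain cutoff is not suitable, because a gestation-at-delivery value may be entered after the birth. Instead:
- prefer a qualifying GEST record dated on or before the outcome to a later one;
- do not count back from the entry date of a post-outcome record;
- for births, where a post-outcome value can be identified as gestation at delivery, count it back from the outcome date; otherwise go on to Steps 3 to 5.

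**Cost.** One condition each in Steps 3 and 4, in text and code. Step 2 needs somewhat more: a rule to identify at-delivery values, which the protocol does not now contain, and the loss of some post-outcome GEST records that cannot be so identified.
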